## Methods

### Study design

This is a randomised, controlled, open-label, parallel-grouped clinical trial. Enrolled participants will be stratified by gender and randomly allocated to one of the following arms:Control group (no intervention)Fruit, Vegetable and Berry (FVB) group, where participants have to ingest an encapsulated fruit, vegetable and berry juice powder concentrate.Omega group, where participants have to ingest an encapsulated plant-based fatty acid supplement.Fruit, Vegetable, Berry and Omega (FVBO) group, where participants have to ingest the fruit, vegetable and berry supplement, together with the plant-based fatty acid supplement.

Randomisation will be performed by a true random number service that generates randomness via atmospheric noise (‘RANDOM.ORG’, Randomness and Integrity Services Ltd., Dublin, IE), by an independent statistician not involved in the recruitment process or analysis of data. In order to ensure a balanced sample size across groups over time, we will stratify by gender and perform block randomisation with a block size of 4. Allocation concealment will be ensured, as the independent statistician will only release the randomisation code to the study team, after a participant is fully enrolled in the study.

The intervention will last 24 months and participants in all groups are advised to continue their habitual diet and lifestyle, throughout the whole duration of the study.

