### Interventions

#### Encapsulated fruit, vegetable and berry juice powder concentrate

The encapsulated fruit, vegetable and berry juice powder concentrate (Juice Plus + ®capsules) is a vitamin- and phytonutrient-rich supplement, derived from 36 dried fruits, vegetables and berries. Participants in the FVB and FVBO groups will be asked to ingest 6 capsules per day, which provide 2910 µg β-carotene, 158mg vitamin C, 18.2mg α-tocopherol equivalents (α-TE, vitamin E), 316 μg folic acid, 6.1mg lutein, 1mg lycopene, > 100 different phenolic compounds and approximately 600mg of polyphenols [29]. Table 1 provides detailed information on the recommended daily allowance (RDA)/ adequate intake (AI)—for available nutrients—contained in the FVB capsules as well as the % RDA/ AI covered by the ingestion of 6 capsules per day, based on the nutrient reference values for the DACH region (collaboration between the German, Austrian and Swiss nutrition societies) [30].

**Table 1 Tab1:** Nutrient reference values and % coverage offered by FVB and Omega capsules

Nutrient	Gender and age range	DACH/EFSA RDA/ AI	FVB (6 capsules)	DACH % RDA/ AI covered by FVB capsules (%)	Omega (2 capsules)	EFSA % AI covered by Omega capsules
β-carotene*	M; 51–65 years	10,200 μg	2910 μg	28.5	–	–
	M; > 65 years	9600 μg	2910 μg	30.3	–	–
	F; > 51 years	8400 μg	2910 μg	34.6	–	–
Vitamin C*	M	110 mg	158 mg	143.6	–	–
	F	95 mg	158 mg	166.3	–	–
α-tocopherol**	M; 51–65 years	13 mg	18.2 mg	140	–	–
	M; > 65 years	12 mg	18.2 mg	151.2	–	–
	F; 51–65 years	12 mg	18.2 mg	151.2	–	–
	F; > 65 years	11 mg	18.2 mg	165.5	–	–
Folic acid*	M & F	180 μg	316 μg	175.6	–	–
EPA + DHA**	M & F	250	–	–	275	110%

*AI* adequate intake, *DACH* Germany, Austria, Switzerland, *DHA* docosahexaenoic acid, *EFSA* European Food Safety Authority, *EPA* eicosapentaenoic acid, *F* female, *FVB* fruit, vegetable and berry, *M* male, *RDA* recommended dietary allowance

*Presented as recommended dietary allowance (RDA)

**Presented as adequate intake (AI)

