#### Encapsulated plant-based fatty acid supplement

The encapsulated fatty acid supplement (Juice Plus + ®Omega Blend) contains plant-based omega fatty acids from algae (*Schizochytrium sp.*) and a variety of seed oils. Participants in the Omega and FVBO groups will be asked to ingest two capsules per day, which provide 375mg of n3 fatty acids [175 mg of DHA, 100mg of EPA, 55mg of docosapentaenoic acid (DPA) and 35mg of α-linolenic acid (ALA)], 250mg of n5 and n7 fatty acids, and 250 mg of n6 and n9 fatty acids. Table 1 provides information on the adequate intake (AI)—for available nutrients—contained in the Omega capsules as well as the % AI covered by the ingestion of 2 capsules per day, based on the nutrient reference values from the European Food Safety Authority (EFSA) [31].

Based on previous experience and in order to increase tolerability, participants are recommended to take capsules with a meal, preferably in the morning and evening. Previous studies have tested the safety of the supplements used and reported no effects on liver, kidney and thyroid function [32, 33].

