At the end of the baseline visit, participants will be randomly allocated to one of the four groups. Participants in the control group will continue with their habitual diet and lifestyle. Those allocated to the three whole food supplement groups, will have to continue their habitual diet and lifestyle, and will also be provided with the corresponding supplements they will have to ingest. Participants will be asked to avoid disposing of any unused capsules and return any leftovers in the next follow-up visit. In addition, all participants will receive a copy of the Wisconsin Upper Respiratory tract Symptoms Survey (WURSS-21) and the Gastro-Intestinal Symptoms Survey-16 (GISS-16) and will be asked to fill these in every time they experience upper respiratory tract or gastrointestinal symptoms, during the duration of the intervention. They will also be reminded that over the following two years they will have to maintain their habitual diet which must correspond to the nutritional inclusion and exclusion criteria.

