#### Follow-up visits

Follow-up visits at 12 and 24 months will be identical to the baseline visit. Follow-up visits at 6 and 18 months will be the same with the baseline visit, with the only exception that the cognitive function test and mtDNA-CN will not be performed. This is due to the fact that we estimate that more than 6-month time would be required to detect any potential changes in these parameters [34].

Participants will be provided with a copy of the food diary they had completed prior to the baseline visit and will be asked to replicate their diet, 4 days before each follow-up visit, to avoid any potential effect of changed nutritional habits on the measured blood markers. They will also be reminded to avoid any strenuous physical activity during this time. At every follow-up visit, we will collect any WURSS-21 and GISS-16 questionnaires completed during the previous 6 months, from participants that experienced respiratory tract symptoms or gastrointestinal discomfort. We will also collect any leftover capsules from the previous 6 months, to monitor intervention compliance. Participants will be contacted via telephone in between visits with a cadence of 3 months, by a member of the research team, to keep them motivated and ensure maximum retention to the trial.

Figure 1 summarises participants’ recruitment and follow-up plan, according to the Consolidated Standards of Reporting Trials (CONSORT) 2010 statement. Figure 2, provides an overview of the schedule of interventions and all study procedures performed at each study visit, according to the Standard Protocol Items: Recommendations for Interventional Trials (SPIRIT) guidelines [35].

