### Statistical analysis

Statistical analysis will be performed using the Statistical Package for the Social Sciences (SPSS) software (version 24.0, IBM Corporation, Chicago, IL) by an independent statistician, blinded to participants’ group allocation. Metric data will be presented as mean ± SD. Statistical significance is set at *P* < 0.05. Normally distributed data fulfilling variance homogeneity will be analysed by one- and two-factorial (either ‘time’ or ‘time x treatment’) repeated measures analysis of variance (ANOVA) and covariance within each group and between all groups. Normal distribution will be determined by the Shapiro–Wilk test and homogeneity of variance by the Levene test. For post hoc analyses we will use the Bonferroni(–Holm) correction and/or Tukey’s post hoc test.

If it is not possible to use metric data, nonparametric tests will be used like the Friedman test (within group) and the Kruskal–Wallis test (between groups). If differences between groups reach significance, the Bonferroni–Holm method will be used to determine the localisation of the differences.

In addition, we will conduct comprehensive correlation analyses to compute relations within each outcome category and between the different outcome categories.

Statistical analyses will include data from all participants with an adherence to the study protocol (intervention compliance) of > 80%.

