## Discussion

To the best of our knowledge, this is the first long-term intervention trial to assess the effect of separate as well as combined ingestions of an encapsulated juice powder concentrate and a plant-based omega fatty acid supplement on biomarkers of cardiovascular health, low-grade inflammation and indicators of ageing in middle-aged and elderly people. Considering that a large proportion of the population already struggles to meet the recommendations on fruit and vegetable and n3 PUFA intakes, whole food-based supplements might play a significant role to reach these targets.

Although the long-term intervention with the fruit and vegetable concentrate supplements and mixed omega fatty acid supplements used in this trial, over two years, has a novel approach and could provide interesting data, it could also have a drawback with regard to product compliance and participants’ commitment to follow-up visits. Nonetheless, we will implement a system of regular communication with the study’s participants in order to keep them motivated and engaged with the study. Additional limitations include the absence of a placebo group and the non-blinded design. However, keeping the study blinded over such a long period of time bears a high risk that participants find out the group they have been allocated to and the placebo group could lose motivation, imposing a compliance problem. We believe that the explorative character of this study, justifies the given design. Finally, although we ask participants to maintain their habitual diet during the entire duration of the study and we ask them to replicate their diet prior to each follow-up visit, there might be cases where participants change their habits considering the long duration of the study. Nevertheless, we do ask about their habits with the use of a questionnaire on every follow-up visit.

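### The one stated analysis population keeps only participants above 80% capsule compliance, a filter that as written acts on the three supplement arms and not on the control arm

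*Protocol article*

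**What the plan says.** All references are to the protocol article.

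- **Population.** After describing the tests, the Statistical analysis section ends with one inclusion rule, limited to no outcome: "Statistical analyses will include data from all participants with an adherence to the study protocol (intervention compliance) of > 80" per cent. No other population is stated.
- **Measurement.** The Follow-up visits section uses the same term for the capsule count: "We will also collect any leftover capsules from the previous 6 months, to monitor intervention compliance". No other measure of intervention compliance is described.
- **Control arm.** Study design gives this arm no intervention, and under Baseline visit: "Participants in the control group will continue with their habitual diet and lifestyle". No compliance percentage is defined for it.
- **Capsule load.** "Participants in the FVB and FVBO groups will be asked to ingest 6 capsules per day", and "Participants in the Omega and FVBO groups will be asked to ingest two capsules per day". The daily load is therefore 2 (Omega), 6 (FVB) or 6 + 2 = 8 (FVBO).
- **Expected difficulty.** The Discussion says of the two-year intervention that "it could also have a drawback with regard to product compliance". It also concedes: "Additional limitations include the absence of a placebo group and the non-blinded design".
- **Sample size.** The section requires 18 per group (omega-3 index) and 19 per group (TNF-α), allows for 30% dropout, and recruits 28 per arm, 112 in total.

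**The concern.** Compliance is observed after randomisation. If inclusion depends on it, the groups analysed are no longer the groups randomised. Here the selection is also uneven. Poor adherers leave the three supplement arms, while their counterparts in the control arm, who would have adhered poorly had they been given capsules, cannot be identified and stay in.

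People who keep taking capsules for two years may differ from those who do not in diet, activity and general health behaviour, all of which could move the biomarkers and cognitive scores under study. With no placebo and no blinding, randomisation is the main protection for the comparison with control, and this rule weakens it. The blinded statistician does not help, because the selection happens before the data are analysed.

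A second issue follows. The sample size has an allowance for dropout but none described for compliance exclusions.

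**Working it through.** **1. The plan's own figure.** 19 / 0.7 = 27.1, rounded up to 28 per arm; 4 × 28 = 112. This reproduces the target. Expected completers per arm are 28 × 0.7 = 19.6, against 19 needed.

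No SD is given, so the 18 and 19 cannot be rebuilt. Working backwards from a two-sided 5% t-test with 80% power, 19 per group implies a standardised difference d of 0.93. For the 0.4 ng/L TNF-α target, the implied SD is 0.4 / 0.93 = about 0.43 ng/L.

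**2. Spurious difference for an inert product.** Inputs assumed, not in the documents:

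- correlation r between adherence tendency and outcome change: 0.1, 0.3 or 0.5
- share q of supplement participants at or below 80% compliance: 20% or 30%
- both variables normal

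Dropping the lowest q of adherers from one arm shifts that arm's mean by r × φ(z_q) / (1 − q) SD, where φ is the standard normal density and z_q its q-quantile.

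- q = 0.20: φ(−0.842) / 0.80 = 0.280 / 0.80 = 0.350
- q = 0.30: φ(−0.524) / 0.70 = 0.348 / 0.70 = 0.497

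The type I error comes from a simulation of 40,000 null trials per row: 20 per arm before filtering, the filter applied to one arm, and a two-sided t-test at 5%.

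| r | q | Shift (SD) | Type I error |
|---|---|---|---|
| 0.1 | 20% | 0.035 | 5.3% |
| 0.1 | 30% | 0.050 | 5.3% |
| 0.3 | 20% | 0.105 | 5.8% |
| 0.3 | 30% | 0.149 | 6.9% |
| 0.5 | 20% | 0.175 | 7.9% |
| 0.5 | 30% | 0.248 | 10.7% |

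At the implied TNF-α SD, the largest shift is 0.248 × 0.43 = about 0.11 ng/L, against the 0.4 ng/L target. A negative r would reverse the sign.

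**3. Numbers analysed.** Assume that compliance exclusions come on top of the 30% dropout, and hold d at 0.93.

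| Completers excluded | Supplement arm | Control arm | Power | Recruits per arm to keep 19 |
|---|---|---|---|---|
| 0% | 19.6 | 19.6 | 81% | 28 |
| 10% | 19.6 × 0.9 = 17.6 | 19.6 | 79% | 19 / (0.7 × 0.9) = 30.2, so 31 |
| 20% | 19.6 × 0.8 = 15.7 | 19.6 | 76% | 19 / (0.7 × 0.8) = 33.9, so 34 |

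**The case against.** **Controls can also break the protocol.** They must keep their habitual diet within the nutritional criteria, repeat the diary diet and avoid strenuous exercise before visits. Adherence to the protocol might be meant to cover this, and a reader who infers that a control could never be excluded on any reading goes too far. But the rule's own parenthesis narrows adherence to intervention compliance, and no percentage is defined for diet or visits. Even the broad reading would exclude people for behaviour after randomisation, by a criterion that differs between arms.

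**A fuller analysis plan may exist.** It may, and the article's silence on an all-randomised analysis carries no weight. The criticism is of the rule that the article does state.

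**Not every comparison is affected in the same way.** This stands. Comparisons between supplement arms filter both sides, though perhaps unequally given the different capsule loads. Within-group analyses over time involve no control. Controls are not unselected either, since dropout is expected in every arm.

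**The bias may be negligible.** This stands as a possibility. At r = 0.1 the error rate is close to nominal. The outcomes are changes from baseline, so stable differences between adherers and others partly cancel. The simulated rates describe one two-arm test, not the planned four-group ANOVA with corrected post hoc tests.

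**The sample-size effect is modest.** This stands. Poor adherers may largely be the people who drop out, and the documents do not separate the two. Even if fully additional, 10 or 20% exclusion costs about 2 or 5 points of power.

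**The trial is exploratory.** The Discussion offers this to justify the open, placebo-free design. It does not justify setting randomised participants aside, and the trial still names co-primary outcomes and a significance level.

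**Conclusion.** The point holds for the rule as written, with high confidence: the stated population selects on behaviour after randomisation, and only the supplement arms can lose participants to it. It should be changed before analysis, because it touches every supplement-versus-control comparison and the results could not show how large the bias was.

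The size is uncertain. A spurious difference of about 0.035 to 0.25 SD, and type I error of about 5 to 11% per two-arm test, rest entirely on the assumed correlations and exclusion rates.

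Two stronger conclusions are tempting and unsupported. One is that the filter must favour the supplements: that requires adherers to do better, which the documents do not establish. The other is that the trial is clearly underpowered: that requires exclusions to be additional to the dropout allowance. What the documents do show is a margin of only 0.6 of a participant per arm (19.6 against 19) and no described allowance for compliance exclusions.

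**What to change.** - Make the primary analysis all randomised participants in their allocated arm, whatever their compliance.
- Replace repeated-measures ANOVA, which in its standard form drops anyone with a missing visit, by a mixed model for repeated measures that uses all available visits. It assumes that data are missing at random, and the plan should say so.
- State that data collection continues for participants who stop or reduce their capsules. The article does not say that they are withdrawn, but the new population depends on their data.
- Keep the above-80% set as a labelled supportive per-protocol analysis, with a stated criterion for controls.

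**Cost.** A short rewrite of the analysis section, with no extra patients or procedures. The effect estimate will be diluted by non-adherers, by an amount that the documents do not give. As an upper bound, if those at or below 80% gained nothing at all, d would fall from 0.93 to 0.93 × 0.9 = 0.84 with 10% of completers non-adherent, or to 0.93 × 0.8 = 0.75 with 20%. Power at 19.6 per arm, by the same t-test calculation, would be about 73% or 63%. Partial compliance should make the loss smaller, and any completers retained beyond the assumed 70% would offset it: with all 28 per arm analysed at d = 0.93, power is about 93%.

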#### Baseline visit

During the baseline visit, the study physician will assess participants’ history once again to ensure that they still fit the inclusion criteria of the study.

Height, weight, BMI and blood pressure will be measured. Participants will be required to fast overnight and fasting blood samples will be collected by venepuncture, to measure biomarkers of cardiovascular health, low-grade inflammation, indicators of ageing, circulating micronutrients and fatty acids.

Following blood drawing, participants will be offered a snack and then asked to complete the cognitive function test (CFD index). Subsequently, they will complete the Short Form survey (SF-36) and the Perceived Stress Scale (PSS-10) questionnaires, which assess quality of life and stress profile respectively. In addition, participants’ physical activity will be assessed via completion of the International Physical Activity Questionnaire—Short Form (IPAQ-SF).

As part of safety routine, we will perform blood analysis including clinical chemistry [i.e. key biomarkers of liver (aspartate transaminase, alkaline phosphatase, gamma-glutamyl transferase) and kidney function (urea, uric acid, creatinine, glomerular filtration rate)], blood proteins, haemogram and coagulation markers. We will also collect the food diary, which was provided to participants during the screening visit, to assess their nutrition and ensure they do not exceed the fruit and vegetable intake, outlined in the inclusion/ exclusion criteria.

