#### Adverse events assessment and reporting

An adverse events reporting system is in place for this study. Any adverse events will be collected after a participant has provided consent and enrolled in the study. The study physician will continuously assess participants’ medical history throughout the study and will refer participants to a specialist expert, should this be necessary. In case the health status of a participant changes during the study or in case of any other concern, the study physician will assess the continuation or withdrawal of the participant from the study.

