#### Gastrointestinal symptoms

For an exploratory assessment of the incidence, duration and severity of gastrointestinal symptoms, the Gastro-Intestinal Symptoms Survey (GISS-16) will be used. The GISS-16 questionnaire was developed based on an adaptation of the WURSS-21. For the needs of this study, the survey includes 16 questions.

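### The > 80% compliance rule makes no exception for tolerability data; applied to GISS-16, it would drop participants whose symptoms caused the low compliance

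*Protocol article*

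**What the plan says.** The Statistical analysis section of the protocol article ends with its only statement on who is analysed: "Statistical analyses will include data from all participants with an adherence to the study protocol (intervention compliance) of > 80" per cent. The sentence is not labelled per-protocol and is not tied to particular outcomes. The article names no other analysis set.

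Compliance is tracked by capsule returns. Under Follow-up visits: "We will also collect any leftover capsules from the previous 6 months, to monitor intervention compliance". No formula or time window is given.

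Three kinds of tolerability or safety data are collected:

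- **GISS-16.** The section on gastrointestinal symptoms gives it an analytic purpose: "For an exploratory assessment of the incidence, duration and severity of gastrointestinal symptoms, the Gastro-Intestinal Symptoms Survey (GISS-16) will be used". Participants in every arm receive the form at baseline, and completed forms are collected at each follow-up visit.
- **Adverse events.** "Any adverse events will be collected after a participant has provided consent and enrolled in the study". No compliance condition is attached.
- **Safety bloods.** Under Baseline visit: "As part of safety routine, we will perform blood analysis including clinical chemistry". No statistical analysis of these as safety data is described.

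The control arm receives no intervention (Study design). Table 2 does not list GISS-16, adverse events or the liver, kidney and blood-count tests as outcomes. PT and PTT appear there, but as primary cardiovascular markers.

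**The concern.** A compliance-restricted set can serve as a supportive efficacy analysis. For tolerability it has a different fault: compliance may be a consequence of the outcome being measured. A participant whose stomach is upset may take fewer capsules, return more of them, miss the cut-off and leave the analysis together with the symptom forms that record the reason.

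The selection acts on one side only. Controls have no capsules to return, so symptoms cannot take a control out by this route. Restricting the capsule arms to people who kept taking the capsules, and comparing them with all controls, pulls the apparent excess of symptoms towards zero and could take it below zero. At stake is whether any statement on two-year gastrointestinal tolerability describes the people allocated to the capsules or only those who tolerated them.

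**Working it through.** The article gives no figure on this point to reproduce. The recruitment target (19 / 0.70 = 27.1, rounded up to 28 per arm; 4 × 28 = 112) reproduces and is not affected.

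**Step 1. Who the rule removes.** Inputs from the Interventions sections and Study design: 6 FVB capsules a day, 2 Omega capsules a day, hence 8 in the combined arm; 24 months. Assumption: compliance is capsules taken divided by capsules due over the 24 months.

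| Pattern | Compliance | Analysed (> 80%)? |
|---|---|---|
| FVB, 5 of 6 daily | 5/6 = 83.3% | yes |
| FVB, 4 of 6 daily | 4/6 = 66.7% | no |
| Omega, 1 of 2 daily | 1/2 = 50% | no |
| Combined, 7 of 8 daily | 7/8 = 87.5% | yes |
| Combined, 6 of 8 daily | 6/8 = 75% | no |
| Full stop at or before 0.80 × 24 = 19.2 months | ≤ 80% | no |
| Full stop after 19.2 months | > 80% | yes |

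The cut-off is reached by quite ordinary reductions, but not by every reduction or every stop.

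**Step 2. Direction of the bias.** Let p be the true symptom incidence in a capsule arm, f the share of symptomatic participants at or below 80%, and g the same share among symptom-free participants. The incidence among those analysed is

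p(1 − f) / [p(1 − f) + (1 − p)(1 − g)].

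This is below p whenever f exceeds g, that is, whenever symptomatic participants miss the cut-off more often than symptom-free ones. The direction needs no further assumption about rates.

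**Step 3. Illustration of size.** All rates here are assumed; none comes from the documents. Take p = 0.35 in the capsule arms and 0.20 in controls, who are not filtered. The true excess is 15 points.

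| f | Analysed incidence, g = 0 | Apparent excess, g = 0 | Apparent excess, g = 0.10 |
|---|---|---|---|
| 0.25 | 0.2625 / 0.9125 = 28.8% | 8.8 points | 11.0 points |
| 0.50 | 0.1750 / 0.8250 = 21.2% | 1.2 points | 3.0 points |
| 0.75 | 0.0875 / 0.7375 = 11.9% | −8.1 points | −7.0 points |

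For g = 0.10 the symptom-free term is 0.65 × 0.90 = 0.585. At f = 0.50, for example, 0.175 / 0.760 = 23.0%, an excess of 3.0 points.

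In numbers of people, f = 0.50 means 28 × 0.35 × 0.50 = 4.9 participants removed per capsule arm.

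**The case against.** The strongest reply is that the closing sentence of the Statistical analysis section governs the analyses described just above it: repeated-measures ANOVA, post hoc tests and correlations among the outcome categories. GISS-16, adverse events and most safety bloods are not in Table 2, so on this reading the rule never reaches them. The article condenses a fuller protocol, where a safety set would normally be defined, and its absence here is not a fault. GISS-16 is described as exploratory, and no safety or tolerability objective is stated.

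Part of this stands:

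- A reader might infer that adverse events and safety bloods are analysed in compliers only. The article does not say so. Adverse events are collected from everyone enrolled, the bloods are described as routine safety monitoring, and a descriptive listing may fall outside the rule.
- A reader might infer that everyone who cuts down or stops is lost. Only those at 80% or below would be.
- The advice on taking capsules with meals ("Based on previous experience and in order to increase tolerability") shows that tolerability was considered. It does not predict that symptoms will lower compliance, nor at what rate.
- GISS-16 forms are collected at visits, so forms from people who stop attending may be lost under any analysis set.

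What does not fall is the wording of the rule. It is stated, not omitted, and it is unqualified. GISS-16 has an explicit aim of assessing incidence, duration and severity in a trial with an untreated arm. An analysis plan that followed the sentence would carry the bias; one that did not would contradict it.

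**Conclusion.** The point holds for GISS-16 and conditionally for the rest. The rule as written has no exception for tolerability data. If it is applied to GISS-16, the capsule-versus-control comparison is biased downwards, provided that symptomatic capsule takers miss the cut-off more often than symptom-free ones. For adverse events and safety bloods the same follows only if they are summarised under this rule, which the article leaves open.

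The amount cannot be estimated from the documents. The table in the working shows only that the distortion could be large relative to the true excess. A reader might take from its last row that the capsules would appear protective; that needs three quarters of symptomatic takers to fall to 80% or below, which nothing in the article supports. The thresholds in Step 1 also rest on an assumed definition of compliance. Because the outcome is exploratory and the remedy is wording, this should be corrected but does not threaten the trial's main comparisons.

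**What to change.** In the Statistical analysis section, limit the > 80% rule to a supportive (per-protocol) efficacy set. Then add, for example: *GISS-16, and any summary of adverse events and safety laboratory values, will be reported for all randomised participants by allocated arm, regardless of compliance, using all data collected up to last contact.*

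This costs one or two sentences. The forms and blood results are already collected, and no visit, assay or extra participant is needed; the target of 112 stands. The downside is that reported symptom rates may look slightly less favourable. The change cannot recover forms that were never returned.
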